## Section 1. Introduction

Anterior cruciate ligament (ACL) injury is one of the most common sports injuries of the knee joint. There is an increasing incidence of ACL injuries, with approximately 60,000 to 200,000 per year in the United States, especially for teenagers. With the incidences of sports injuries increasing gradually in China, the public have paid more attention to the functional recovery of sports activities, and ACL reconstruction (ACLR) has become a conventional surgery performed in sports medicine. In ACLR, autologous tendons are usually harvested and prepared into several-stranded grafts, which are passed through the tibial and femoral tunnels and fixed by suspension or extrusion. Afterwards, the grafts undergo a series of biological tendon-to-bone healing processes (termed “ligamentization”, a transformation from tendons to the functional ACL), including avascular necrosis in the early healing stage, proliferation and revascularization in the remodeling stage, and restoration of histological and biomechanical properties in the maturation stage. Factors associated with unfavorable graft remodeling and maturation (biological recovery) after ACLR include graft impingement, sports reinjury, and residual knee laxity. Furthermore, edema and adhesions are common postoperative reactions, causing symptoms of knee swelling, pain, and limited range of motion as well as hampering the functional recovery. To prevent the development of adverse outcomes (such as graft failure, arthrofibrosis, and osteoarthritis), timely intervention should be taken, including medications, physical therapy, and arthroscopic surgeries.

Platelet-rich plasma (PRP) is a biological product made from autologous blood through centrifugation and degranulation steps, with good records of safety and promising efficacy in therapy for musculoskeletal disorders. The platelet concentration of PRP is about 3–5 times that of whole blood, with enrichment of growth factors and cytokines; hence, PRP is widely recognized to have a potential for promotion of healing after tissue injury or repair, which has attracted the interest of researchers in orthopedics and sports medicine. Cell and animal studies have shown that PRP can promote skeletal muscle regeneration, reduce cell apoptosis, regulate tissue differentiation, and inhibit adhesion and fibrosis. When it comes to clinical application, the actual effect of PRP is controversial. Systematic reviews have demonstrated that PRP injection resulted in clinical improvements in patients with lateral epicondylitis and knee osteoarthritis, with regard to ACLR, the application of PRP-pretreated grafts was ineffective in promoting graft-to-bone healing and preventing tunnel widening, while intraoperative injection of PRP in the graft harvesting area and bone tunnels may help reduce donor site pain and promote graft revascularization, respectively. It can be seen that the actual effect of PRP depends on the timing, locations, and methods of administration. Based

on the promising biological effects and good safety records of PRP in basic scientific research and clinical practice, we hypothesize that injecting the PRP into the joint cavity at fixed intervals after ACLR may result in reduction in knee symptoms related to edema and adhesion reactions as well as promotion of graft revascularization.

In terms of research feasibility, the principal investigator is an experienced orthopedic surgeon specialized in knee arthroscopic surgeries and expertized in clinical study design; the annual amount of ACLR surgeries performed in the department of sports medicine in our institution is at the leading level throughout the country; the standard operating procedures (SOP) for ACLR, postoperative rehabilitation, and PRP preparation and injection have been formulated and generalized according to high-level evidence as well as clinical practice. Investigators in the research group have been engaged in basic and clinical studies related to ACL injury and reconstruction for many years, with proficiency in patient recruitment, informed consent, follow-up visiting, outcome measurements and statistical analyses.

## **Section 2. Purposes**

The main purpose of this study is to evaluate the clinical efficacy of postoperative intra-articular PRP injection on subjective outcomes (overall perception of pain, symptoms, function in sports activities, and quality of life) in patients with ACLR.

The secondary purposes of this study are to evaluate the various clinical and radiological outcomes (including pain, swelling, adhesion, and graft revascularization and maturation) during the first year after ACLR with or without postoperative intra-articular PRP injection.

## **Section 3. Study Design**

This study is a prospective, single-blinded, randomized controlled trial to perform in a single center (Department of Sports Medicine, Shanghai Sixth People's Hospital).

## **Section 4. Study Population**

### **4.1 Inclusion Criteria**

Participants included in the study should meet all the following criteria:

- ① Patients with ACL injury diagnosed by radiology or under arthroscopy who are scheduled to undergo ACLR;
- ② Aged 16–45 years old with epiphyseal closure of the femur and tibia;
- ③ The range of motion of the affected knee is nearly normal before the operation (reaching nearly full knee extension and bending over 120°);
- ④ Volunteer to participate in the research and sign the informed consent.

## **4.2 Exclusion Criteria**

Patients screened for eligibility should be excluded if they meet any of the following criteria:

- ① Multiple ligament injuries caused by severe trauma (including posterior cruciate ligament injury, posterolateral complex injury, medial patellofemoral ligament injury, and grade 2 or 3 medial collateral ligament injury);
- ② Bilateral ACL injuries or contralateral knee dysfunction;
- ③ Combined with tibial plateau fracture, severe cartilage damage or defect, meniscus repair, or knee osteoarthritis;
- ④ History of the knee joint surgery (ipsilateral and contralateral);
- ⑤ Combined with systemic diseases, such as malignant tumors, blood system diseases, rheumatic diseases, and endocrine or metabolic diseases;
- ⑥ History of infectious diseases transmitted through blood, such as an infection of human immunodeficiency virus, hepatitis B or C virus, or treponema pallidum;
- ⑦ Children under 16 years old, or women in pregnancy and lactation;
- ⑧ History of drug and alcohol abuse, cognitive dysfunction, or mental illness;
- ⑨ Other conditions that affect the cooperation with postoperative treatment, rehabilitation, and completion of follow-up visits.

## **4.3 Criteria of Protocol Violation**

Participants included in the study should be classified as protocol violation (not excluded in the intention-to-treat analysis but excluded in the per-protocol analysis) if they meet any of the following criteria:

- ① Participants in the intervention group who fail to receive the intervention protocols (receiving 0, 1, 2, or >3 doses, or 3 doses with violation of injection schedules);
- ② Participants in both groups who undergo reoperation (including debridement, lysis of adhesion, revision ACLR, and other knee surgeries) or receive knee injection out of the protocol (including PRP, sodium hyaluronate, and other medications).

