#### **4.4 Criteria of Dropout**

Participants included in the study should be classified as dropout (with missing data but not excluded in the analyses) if they meet any of the following criteria:

- ① Lost to follow-up during the study period;
- ② Request to withdraw the informed consent;
- ③ Other circumstances that affect the completion of follow-up visits.

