## **Section 8. Intervention and Control**

### **8.1 Intervention**

Participants allocated to the intervention group will receive blood withdrawal followed by PRP injection at 4 weeks ( $\pm 3$  days), 8 weeks ( $\pm 5$  days), and 3 months ( $\pm 7$  days) during the routine follow-up visits (after clinical assessments) following the standardized protocol:

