## 8.2 Control

Participants allocated to the control group will undergo the same timing and assessments of follow-up visits without postoperative knee injection. Participants in both groups should avoid co-interventions which may cause confounding biases, including unscheduled knee injection and non-steroidal anti-inflammatory drugs, while acetaminophen can be prescribed for participants who report a moderate to severe pain if required (should be suspended for 7 days before clinical assessments). If participants receive additional medications or treatment out of the protocol, they should report them completely to the clinicians at follow-up visits.

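### The per-protocol set filters the PRP arm on punctual attendance at three visits but sets no attendance rule for controls, and 4.3 and 12.2 disagree on participants who received no dose

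*Protocol*

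**What the plan says.** Section 4.3 gives two violation criteria. Both keep a participant in the intention-to-treat analysis and remove him or her from the per-protocol analysis. The first applies to the intervention group alone: "Participants in the intervention group who fail to receive the intervention protocols (receiving 0, 1, 2, or >3 doses, or 3 doses with violation of" the schedule. The second opens with "Participants in both groups who undergo reoperation" and adds knee injections outside the protocol. It says nothing about visits.

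Section 8.1 schedules the PRP injections at 4 weeks (±3 days), 8 weeks (±5 days) and 3 months (±7 days), given "during the routine follow-up visits (after clinical assessments"). Section 8.2 says that controls "will undergo the same timing and assessments of follow-up visits without postoperative knee injection". Under 4.4 a participant who does not complete follow-up is "classified as dropout (with missing data but not excluded in the analyses"), which is a separate category from protocol violation.

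Section 12.2 places the per-protocol analyses of all outcomes among the sensitivity analyses and bases them on the 4.3 criteria. It also labels them as-treated, and it moves a participant whose care matched the other arm's protocol exactly into that arm.

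**The concern.** Because each injection happens at a routine visit, the dose rule is also an attendance rule. A PRP participant who misses one of the three visits, or comes a day outside the window, leaves the per-protocol set. A control who does the same stays in.

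Attendance is behaviour after randomization. If people who keep appointments also follow rehabilitation better and report better KOOS4 at 12 months, filtering one arm on attendance produces a difference without any treatment effect. The ANCOVA covariate is baseline KOOS4 (12.1), which does not adjust for later adherence. At stake is whether agreement between the per-protocol and primary results would mean what readers will take it to mean.

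**Working it through.** **1. The rules side by side**

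| Event | PRP participant | Control |
|---|---|---|
| Misses the 4-week, 8-week or 3-month visit | Fewer than 3 doses, or a dose off schedule: removed (4.3, first criterion) | No criterion: stays |
| Attends outside the window | Dose off schedule: removed | No criterion: stays |
| Attends but declines the injection | Removed | No counterpart |
| Reoperation or off-protocol knee injection | Removed | Removed |
| No 12-month KOOS4 | Contributes nothing: no imputation in the primary analysis (12.1), same methods per protocol (12.2) | Same |

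The first two rows are the asymmetry. It acts on participants who deviated early but still returned at 12 months.

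**2. Illustrative size**

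The plan gives no figure for this bias. Let p be the share of the PRP arm removed for missed or late visits, and d the amount by which they score below the rest. Neither is in the documents; both are assumptions. With no treatment effect and the same mix in both arms:

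- Mean of each full arm: (1 − p)·m + p·(m − d) = m − p·d
- PRP mean after removal: m
- Spurious difference: p·d

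With p = 0.10 and d = 5: 0.10 × 5 = 0.5 points, and 0.5/13 = 3.8% of the 13-point MCID. With p = 0.25 and d = 10: 0.25 × 10 = 2.5 points, and 2.5/13 = 19.2%.

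**3. Cross-check with the plan's own SD and sample size**

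Section 5 reproduces: effect size 13/20 = 0.65; a two-sample t test at 2-sided 0.05 and power 0.9 needs 50.72, so 51 per group; 51/0.85 = 60. That figure is not in dispute and only supplies SD 20 and n = 51.

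Suppose that adherence is a normal trait with correlation r to 12-month KOOS4, and that the least adherent share q is removed from the PRP arm only. Then bias = r × 20 × φ(z_q)/(1 − q), where z_q is the q-quantile of the standard normal. For q = 0.1 and r = 0.5: 0.5 × 20 × 0.1755/0.9 = 1.95. Rejection rates come from 20,000 simulated trials per scenario, 51 per arm before removal, no true effect, t test without covariate.

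| q | Bias at r = 0.1 / 0.3 / 0.5 (points) | Rejection at nominal 5% |
|---|---|---|
| 10% | 0.39 / 1.17 / 1.95 | 5.2% / 6.0% / 7.6% |
| 20% | 0.70 / 2.10 / 3.50 | 5.4% / 7.8% / 13.2% |
| 30% | 0.99 / 2.98 / 4.97 | 5.7% / 10.4% / 20.7% |

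With the same filter in both arms, bias is about 0 and rejection 4.9% to 5.0%. That follows from assuming the same selection mechanism in both arms, so it is a best case for the fix.

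**4. Zero-dose participants**

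Section 4.3 removes a PRP participant with 0 doses. Section 12.2 could count the same person as a control, at least one who attended and was not injected. Assume that half of the non-adherent PRP participants are moved: 51 × q × 0.5 people with mean −r × 20 × φ(z_q)/q join 51 controls. The bias becomes 0.56 to 2.79 points at q = 10% and 1.30 to 6.48 at q = 30%, for r from 0.1 to 0.5.

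**The case against.** The best defence is that a per-protocol set asks whether the assigned treatment was received. For PRP that means three scheduled injections; for control, no knee injection. A control who comes a few days late has still received the control condition, so some asymmetry follows from the design. This stands in part: a dose declined at an attended visit has no control counterpart. The attendance component, however, can be mirrored, because 8.2 gives controls the same visits.

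The magnitude is also open to challenge. Nothing in the documents supports a 5 to 10 point gap for someone slightly late. The 0.5 to 2.5 points lie below one standard error of the difference, 20 × √(2/51) ≈ 4.0, and the larger simulated effects need heavy exclusion together with strong correlation. All of this stands.

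Several stronger readings are tempting, and the documents do not support them:

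- *The controls are unselected.* They are unselected on attendance only. Reoperation and off-protocol injection remove them as they do PRP participants, and the last exclusion criterion in 4.2 screens both arms for conditions that hinder follow-up.
- *The bias must favour PRP.* Some participants may skip a dose because they feel well, which would push the other way.
- *The main result is compromised.* The primary analysis is intention-to-treat (12.1), and no decision rule in the protocol rests on the per-protocol result.
- *Matched windows would remove the bias.* Participants know their allocation once it is revealed at the first follow-up visit (7.2). From then on, the PRP arm attends for blood withdrawal and injection and the controls for assessment only, so attendance need not select the same people in each arm.

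**Conclusion.** The asymmetry is in the text and no other section cures it: attendance is filtered in the PRP arm only. The consequence is confined to the per-protocol sensitivity analyses. A bias towards PRP is plausible if punctual attenders do better, but that is an assumption. So is the size: 0.5 to 2.5 KOOS4 points for p of 10% to 25% and d of 5 to 10 points, or about 0.4 to 5.0 points in the correlation model with q of 10% to 30% and r of 0.1 to 0.5. All of these are below the 13-point MCID. The conflict between 4.3 and 12.2 over zero-dose participants is a separate textual defect that could enlarge the bias. The point deserves correction because the correction is cheap and the analysis is meant to test the robustness of the primary result.

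**What to change.** 1. In 4.3 and 12.2, define the per-protocol set with the same attendance rule in both arms. A control qualifies only if he or she attended the 4-week, 8-week and 3-month visits within the ±3, ±5 and ±7 day windows that 8.1 already sets, and received no knee injection. The reoperation criterion stays common to both arms. This changes an analysis set, not treatment.
2. State beside the definition that this reduces selection bias but does not remove it, since refusal of a dose at an attended visit has no control counterpart and participants know their allocation.
3. Reconcile 4.3 with 12.2 so that non-adherent PRP participants are not counted as controls in the per-protocol analysis. If a true as-treated comparison is also wanted, define and report it separately.

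The cost is a few sentences, a somewhat smaller control per-protocol set, and the need to capture control visit dates at the scheduled assessments. The protocol does not say that these dates are recorded, and it states windows only for the injections. An adherence-adjusted estimator (inverse-probability weighting or a complier average causal effect) could be used instead, but it needs further assumptions of its own.

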## **Section 11. Adverse Events**

### **11.1 Definition and Classification**

Adverse event (AE) refers to any unfavorable and unintended sign (including an abnormal laboratory finding), symptom, or disease temporally associated with the use of a medical treatment or procedure in a patient or clinical investigation subject, whether or not related to the medical treatment or procedure. AEs are usually graded by the severity:

- ① Mild AEs: asymptomatic or mild symptoms; observations only; intervention not indicated.
- ② Moderate AEs: minimal or local intervention indicated; limiting instrumental activities.
- ③ Serious AEs (SAEs): AEs that (1) results in death, (2) is life-threatening, (3) requires inpatient hospitalization or causes prolongation of existing hospitalization, (4) results in persistent or significant disability, (5) may have caused a congenital anomaly or birth defect, or (6) requires intervention to prevent permanent impairment or damage.

In this study, the AEs are classified into intervention-related AEs (only occurrence in intervention group and probably related to the intervention) and common AEs (occurrence in both groups, whether or not increased with intervention). Possible intervention-related AEs include fainting, allergic reaction, pain at injection site, knee swelling, decreased range of motion, and infection at injection site. Because of the study population (patients with ACL injuries and undergoing ACLR), common AEs should include all complications and unfavorable outcomes accompanied with ACL injuries as well as those with ACLR, such as graft failure, residual laxity, decreased range of motion, and arthrofibrosis.

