## **Section 12. Statistical Analysis**

### **12.1 Primary Analysis**

The primary analysis will be performed following the intention-to-treat principle, which emphasizes on the original group allocation by randomization. Specifically, once a participant is enrolled and undergoes randomization, the baseline and outcome measures will be included in the allocated group, regardless of whether the participant violates the protocols and whether the participant is dropout during follow-up: (1) if a participant is randomized to the intervention group but does not receive 3 doses of PRP injection, this participant will not be

excluded from the intervention group; (2) if a participant is randomized to the control group but receives knee injection out of the protocol, this participant will not be excluded from the control group; (3) if a participant is randomized to either group but lost to follow-up, this participant will not be excluded from the primary analysis, either. In principle, the primary analysis should include all participants randomized in this study. For the missing data, simple or multiple imputation will not be performed in the primary analysis.

All statistical analyses will be performed using the IBM SPSS software, with a 2-sided significance level of 0.05. Descriptive statistics will be presented as mean and SD (for normally distributed values), median and interquartile range (for non-normally distributed values), or number and percentage (for categorical variables).

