#### ③ Other variables

The Kolmogorov-Smirnov test will be applied to evaluate the normality for continuous variables. The Student t test will be used for comparison of continuous variables with normal distribution. The Mann-Whitney-Wilcoxon test will be used for comparison of non-normally distributed continuous variables and ordinal variables (including GROC, amount of ACL

remnant, and grades of knee laxity). The Pearson chi-square test or Fisher exact test will be used for comparison of categorical variables (including demographic data and adverse events), depending on expected frequencies for the contingency tables.

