## **12.2 Post-hoc Sensitivity Analyses**

For all outcomes with missing data, the number, proportion, and reasons of patients who are not available for the outcome should be reported. For any outcome with missing data >5%, multiple imputation by chained equations (fully conditional specifications method) should be performed with 20 iterations to evaluate the bias caused by non-random missing and detect any change towards a different direction of the significance level. Variables in the imputation model should include group allocation, age, gender, sports participation, graft diameters, meniscal treatment, and baseline KOOS4 (or corresponding baseline evaluation, if applicable). These variables are potential predictors and confounders of clinical outcomes and may also be explored in multivariate linear regression analyses to quantitatively compare the effects of different factors associated with the clinical outcomes.

Furthermore, per-protocol (as-treated) analyses for all outcomes should be performed based on the criteria of protocol violation. In this context, participants who receive reoperation or any unscheduled knee injection (more, less, or violation of injection schedules) should be excluded from the originally randomized group. In particular, if a participant is found out to receive the intervention or control following exactly the same protocol as the opposite group, this participant should be included in the opposite group. Per-protocol analyses will follow the above-mentioned statistical methods in the primary analysis.

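### The per-protocol sensitivity analysis has no safety exception, so its adverse-event comparison would drop reoperated participants and those who stopped PRP early

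*Protocol*

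**What the plan says.** Protocol Section 4.3 has two criteria for a protocol violation. The first applies to the PRP arm only and covers 0, 1, 2 or more than 3 doses, or three doses off schedule. The second applies to both arms and covers "Participants in both groups who undergo reoperation (including debridement, lysis of adhesion, revision ACLR, and other knee surgeries", as well as knee injections outside the protocol. Violators are "not excluded in the intention-to-treat analysis but excluded in the per-protocol analysis".

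Section 12.2, headed "Post-hoc Sensitivity Analyses", states that "per-protocol (as-treated) analyses for all outcomes should be performed based on the criteria of protocol violation". It repeats that "participants who receive reoperation or any unscheduled knee injection (more, less, or violation of injection schedules) should be excluded from the originally randomized group", and says that these analyses use the statistical methods of the primary analysis.

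Section 12.1 is the intention-to-treat analysis: "In principle, the primary analysis should include all participants randomized in this study". Its part on other variables assigns the chi-square or Fisher test to "comparison of categorical variables (including demographic data and adverse events".

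The visit table in Section 9 places adverse events under its outcome-measures heading. Section 11.1 gives examples of common adverse events, "such as graft failure, residual laxity, decreased range of motion, and arthrofibrosis", and lists fainting, allergic reaction and injection-site infection among the possible intervention-related ones.

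**The concern.** Reoperation happens after randomisation, and here it is often the treatment of a complication. Lysis of adhesion answers arthrofibrosis, and revision ACLR answers graft failure. A participant can take all three doses on time, or be a fully compliant control, and still become a violator through a late revision. Excluding that person from an adverse-event comparison selects on the event being compared.

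The dosing criterion raises a related problem for harms. A PRP participant who stops after one or two doses because of a reaction leaves the per-protocol set, and the reaction leaves too. For efficacy this is what a per-protocol set is meant to do. For safety it removes the people who tolerated the injection worst, and it can do so only in the PRP arm.

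At stake is a safety table with few or no surgical complications and little intolerance. A reader could take it as reassurance when the exclusion rule produced it.

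**Working it through.** **1. Is there a figure of the plan to reproduce?** None depends on this rule. The sample size (difference 13, SD 20, two-sided 0.05, power 0.90) reproduces with the two-sample t-test: 50.72, rounded up to 51 per group. Then 51/0.85 = 60 per group, 120 in total. The reoperation rule does not touch it.

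**2. Do adverse events fall within the per-protocol scope?**
- Section 12.2 covers every outcome and names no exception.
- Section 9 lists adverse events as an outcome measure.
- Section 12.2 takes over the methods of 12.1, and these include the test of adverse events.
- Section 10 does not list adverse events; they have their own Section 11.

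The literal reading includes them, and nothing in the text excludes them.

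**3. Who is removed?**
- *Reoperated, either arm:* removed by 4.3 and 12.2, together with all their adverse events.
- *Complication managed without surgery:* stays, unless another violation applies. Section 1 names medication and physical therapy as well as arthroscopic surgery for such outcomes.
- *PRP participant who stops after one or two doses:* removed. The 12.2 clause that moves a participant to the opposite group requires having followed that group's protocol exactly, so it does not bring this person back.

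The removed cases are likely to be the graver ones. By Section 11.1, an event that requires hospital admission, or intervention to prevent permanent impairment, is serious, and many reoperations would meet that definition.

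**4. Effect on counts (assumed, since the documents give no rate).** Take 5/60 reoperated in one arm and 2/60 in the other: 5/60 = 8.3% and 2/60 = 3.3%. If there are no other violations, the per-protocol sets are 60 − 5 = 55 and 60 − 2 = 58, with 0 reoperated in each. The zero follows from the definition, whatever the true rates.

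**5. Effect on KOOS4 (assumed).** Let *r*P and *r*C be the reoperation rates, and L the 12-month score loss in reoperated participants. Assume no treatment effect in the rest and no other violations, and ignore the baseline adjustment. Then

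intention-to-treat difference (PRP − control) = −(*r*P − *r*C) × L; per-protocol difference = 0.

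| Rates, PRP vs control | Reoperated | L = 10 | L = 20 | L = 30 |
|---|---|---|---|---|
| 5% vs 5% | 3 vs 3 | 0 | 0 | 0 |
| 10% vs 5% | 6 vs 3 | −0.5 | −1.0 | −1.5 |
| 15% vs 5% | 9 vs 3 | −1.0 | −2.0 | −3.0 |

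With the arms reversed, the signs reverse. The rule can therefore hide benefit as well as harm.

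**The case against.** The strongest reply is that no harm is lost where it counts. Section 4.3 itself keeps violators in the intention-to-treat analysis, and the adverse-event test is written into 12.1. Section 11.2 requires every adverse event to be recorded, and Section 13 requires a complete analysis of adverse events for the review board. All of this stands. A reader might infer from 4.3 that graft failure, arthrofibrosis and infection disappear from the trial's safety comparison; the documents do not support that. Nor does every such case leave the per-protocol set, since the second criterion removes only those reoperated.

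It can also be said that Section 10 omits adverse events, so 12.2 may never have been meant to cover them. That makes the scope arguable but does not settle it: Section 9 points the other way, and 12.2 is silent.

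A third reply is that reoperation is a legitimate per-protocol exclusion for efficacy. After revision ACLR, the 12-month graft signal describes a different graft, and a second operation affects KOOS and range of motion. This has force, so it does not follow that reoperation must be struck from 4.3. The opposing argument is that laxity and range of motion are secondary outcomes, and that dropping people who needed revision or lysis selects on the consequences of what these outcomes measure. That is a trade-off to be judged, not an error.

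Finally, the lack of a dosing criterion for controls is no fault in itself. Controls have no doses to miss, and their departure, an unscheduled injection, is covered by the second criterion.

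**Conclusion.** The point holds, confined to the per-protocol sensitivity analysis. As written, Section 12.2 calls for a per-protocol comparison of adverse events in a set from which 4.3 has removed participants because a complication led to surgery or, in the PRP arm, because a reaction cut the injections short. That comparison cannot be read as evidence on safety. The primary KOOS4 result, the main adverse-event comparison and the sample size are unaffected.

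For reoperated participants the loss from the per-protocol counts is complete by definition. How many that means cannot be stated, because the documents give no rate. For KOOS4, the hidden difference is about 0.5 to 3 points under assumed unequal rates between 5% and 15% and an assumed loss of 10 to 30 points. That is small against 13, and it is zero if rates and losses are equal across arms. The conclusion rests on reading the scope of 12.2 to include adverse events, which Section 9 supports.

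**What to change.** In Section 12.2, change the scope of the per-protocol analyses from all outcomes to efficacy outcomes.

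In the same place, state that:
- adverse events are analysed in all randomised participants by allocated arm, with reoperation reported by arm as a safety outcome;
- a supporting safety table by treatment received counts anyone given at least one PRP injection as exposed, including those who stopped early.

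Whether reoperation remains a per-protocol exclusion for efficacy outcomes is for the sponsor to decide. If it remains, report the number excluded for it in each arm beside every per-protocol result, so that an imbalance is visible.

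The cost is a few sentences and one extra safety table. No new data are needed, because Section 11.2 already has adverse events and their treatment recorded.
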